### Power analysis and target population

Using the Hedeker et al. approach [52], for a test of a between groups linear trend difference (comparing normal infant growth to those with RWG), equal sample sizes, 6 time points, a correlation among the repeated measures of 0.5, a compound symmetry structure, a medium effect size of one third of a standard deviation, an α of 0.05, and a power of 0.8, a total sample size of 184 participants (includes for estimated 20% attrition) is needed for Aim 1. To power for Aims 2–3, we reduced all EMG constructs (Fig. 1) into a single virtual covariate to facilitate computation. We then generated simulated data based on a mixed effect logistic regression model that included the virtual covariate, a sleep pattern variable and a GM diversity variable, each randomly drawn from a normal distribution and having six repeated measures. We fixed the effect size of the virtual covariate to be medium (Cohen’s f2 = 0.15), and varied the effect sizes of the sleep pattern variable and the GM diversity variable between medium (f2 = 0.15) and large (f2 = 0.35) as were observed in unpublished preliminary data. Figure 2 shows that 160 infants are required to achieve a power of 0.8 to detect a significant medium-sized effect at α = 0.05. Adjustment for a 20% attrition rate requires that we recruit 192 mother-infant pairs.

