### Statistical analyses

To evaluate Aim 1, visit-to-visit changes in 24 h sleep and sleep-wake rhythmicity variables and their relationship to occurrence of RWG will be examined with a logistic TVEM. It can reveal critical periods during which changes in sleep-wake patterns accelerate/decelerate infant weight gain [114] and include other covariates with time-invariant effects. The TVEM model can be formulated as,

1$$ logit\;(RWG)={\beta}_0f(t)+{\Sigma}_v\kern0.5em {\beta}_vf(t)V+{\Sigma}_c\kern0.5em {\beta}_cC+\in $$where *f*(*t*) is a smooth function of time *t*, *V* is a set of variables with time-varying effects, *C* is a set of variables with time-invariant effects, *β*_0_, *β*_*v*_ and *β*_*c*_ are the corresponding coefficients, and *ϵ* is normally distributed random errors. We will impose no constraints on the *f*(*t*) function and the *β* coefficients except an assumption of smooth temporal progressions. To fit the model given the collected data, we will use the %TVEM SAS macro [115] and use a P-spline method to select the best-fitting model using knots (splitting points). Significance will be assessed based on the *p*-values of estimated *β* coefficients.

To evaluate Aim 2, we will apply the TVEM in model (1) with representing the alpha and beta diversity scores for each taxon. Because there are hundreds of taxa that may share dependencies, we will compute false discovery rates (FDRs) using the Benjamini–Hochberg procedure [116]. Taxa with FDR < 5% will be regarded as having significant associations. Given the hierarchical structure among taxa, we will further reduce the redundancies among significant taxa by ranking them on Akaike information criterion (AIC) values. Specifically, we will traverse the taxonomic tree (leaves to root) and compute AIC values for each clade. If a parent node has a lower AIC value than any of its child nodes, we will keep the parent node and remove the child nodes from the short-listed taxa.

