
Some potential challenges should be acknowledged. Recruitment and retention of participants in longitudinal research is often challenging. To address this challenge, at recruitment and each in-home visit, we will offer “swag” bags with items of interest to pregnant and postpartum mothers and their infants. Regular contact with a designated staff member will establish strong relationships to help aid retention over the study period of 12–15 months*.* We will further incentivize regular contact for each answered call, every time a mother notifies the team of a change in contact information, and for each 24-h dietary recall completed by phone. Mothers will be reminded by telephone or postcard of their next scheduled home visit. We will also send participants birthday, major holiday, and Mother’s Day cards. Further, mothers will be given the opportunity to opt-in to a study-developed, social media-based community of other participants to share in their experiences as mothers of young children. Additionally, sampling bias might occur if individuals worry about the risks of in-home visit due to the COVID-19 pandemic and shy away from participation. In order to minimize the risk of sampling bias and maximize the validity of the study, recruitment efforts will emphasize the numerous safety precautions and social distancing measures that the study can employ to minimize any in-person interactions. Lastly, mothers might hesitate to collect fecal and other biobehavioral measures. The research team has prepared and uploaded written and video instructions to the study website, including the guidelines to collect all biospecimens at home for mothers and infants. Additionally, nitrile gloves will be provided for mothers to use when collecting biological specimens, and proper hand washing instructions will be provided to minimize the risk of fecal bacterial exposure.

Through the identification of optimal and crucial developmental intervals for targeting and preventing RWG, this observational, longitudinal study will provide evidence to spur the development of theoretical and data-driven interventions to prevent RWG and subsequent obesity, and clinical practice guidelines that address modifiable factors that influence sleep-wake and GM development in support of optimal metabolic and growth outcomes.

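### Aim 1 promises critical periods for sleep, but its only stated test is of no effect, which cannot show that the effect differs by age

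*Protocol article*

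**What the plan says.** For Aim 1, the Statistical analyses section relates the sleep and rhythm variables to rapid weight gain (RWG) in a logistic TVEM, model (1), and says of it: "It can reveal critical periods during which changes in sleep-wake patterns accelerate/decelerate infant weight gain". The model separates variables V, whose effect may change with age, from variables C, whose effect is fixed.

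Three sentences govern shape and inference:

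- On shape: "We will impose no constraints on the *f*(*t*) function and the *β* coefficients except an assumption of smooth temporal progressions".
- On model selection, the authors will "use a P-spline method to select the best-fitting model using knots (splitting points").
- On inference: "Significance will be assessed based on the *p*-values of estimated *β* coefficients".

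The Discussion closes with the intended use: "Through the identification of optimal and crucial developmental intervals for targeting and preventing RWG", the study is to inform interventions and practice guidelines.

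For Aim 3, by contrast, synergy between sleep and gut microbiota is to be judged from the interaction terms, that is, from a test aimed at the claim being made.

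**The concern.** Two different questions are involved. One is whether sleep is associated with RWG at all, with null β_v = 0. The other is whether the association is stronger at some ages than at others, with null β_v(t) equal to one constant. A critical period is a claim of the second kind, and the only stated rule addresses the first. An effect that is significant at 8 weeks and not at 9 months has not been shown to differ between those ages. Choosing knots for best fit is not a test of constancy either.

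What is at stake is the timing message. An intervention could be aimed at a window that is only the part of a flat curve that happened to cross the 5% line, although timing made no difference. The rates below are per sleep variable. The article lists five primary actigraphic sleep variables and several rhythm variables, so there are many chances for such a window.

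**Working it through.** **Inputs from the protocol (Power analysis and target population).** One third of an SD; six time points; correlation 0.5 with compound symmetry; α 0.05; power 0.8; 184 for Aim 1 and 192 recruited, with 20% attrition. Retained infants: 184 × 0.8 ≈ 147 and 192 × 0.8 ≈ 154.

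**Assumptions not in the protocol.** RWG prevalence 0.2 to 0.5 (0.5 corresponds to the equal groups of the power analysis), and a normally distributed sleep measure.

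**Step 1: the plan's own figure.** For a difference δ that is the same at all six visits, n per group = 2(z₀.₉₇₅ + z₀.₈₀)² × v/δ². Here v is the variance of the six-visit mean, with retention r falling evenly from 1.00 to 0.80:

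v = [0.5 × Σ(1/r) + 0.5 × (Σ1/√r)²]/36 = [0.5 × 6.705 + 0.5 × 40.174]/36 = 0.651

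n = 2 × 7.849 × 0.651 × 9 = 91.99, so 92 per group and 184 in total. This matches the protocol.

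The protocol describes the calculation as being "for a test of a between groups linear trend difference". A two-sided trend from 0 to one third of an SD gives 230 instead. That is a side matter and nothing below depends on it. One third of an SD, held constant over age, is the test case used here.

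**Step 2: effect on the logistic scale.** For a normal exposure with equal variances, the log odds ratio per SD equals the standardised mean difference. A difference of 1/3 SD gives OR = exp(1/3) = 1.40 per SD.

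**Step 3: hand check at a single visit.** SE ≈ 1/√(N p(1 − p)). With N = 154:

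| RWG prevalence p | log OR | SE | z | chance of significance |
|---|---|---|---|---|
| 0.2 | 0.333 | 0.201 | 1.65 | 38% |
| 0.3 | 0.333 | 0.176 | 1.90 | 47% |
| 0.5 | 0.333 | 0.161 | 2.07 | 54% |
| 0.3 | 0.693 (OR 2) | 0.176 | 3.94 | 98% |

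At the Aim 1 effect size, significance at any one age is close to a coin toss, so it will often come and go along a flat curve. At OR 2 it rarely does.

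**Step 4: simulation.** 4,000 runs per setting, six ages, log OR 1/3 at every age, correlation 0.5, N 147 to 184, prevalence 0.2 to 0.5. The fitted model is a logistic varying-coefficient model with infant-clustered covariance. An apparent window means that β(t) is significant pointwise at some ages but not all. The constancy test is a joint Wald test that β(t) is the same at all ages.

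| Form of β(t) | Apparent window | Constancy test rejects | Window and rejection |
|---|---|---|---|
| Linear in age | 28-35% | 4-6% | 3-4% |
| Quadratic | 44-52% | 5-7% | 4-6% |
| Free by visit | 68-73% | 5-8% | 5-8% |

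**Step 5: sensitivity.** At N 154 and prevalence 0.3, moving the correlation from 0.3 to 0.7 takes the apparent-window rate from 62% to 37% (quadratic) and from 82% to 55% (free by visit). With a constant OR of 2 per SD it is about 1-14%. I confirmed this last range at prevalence 0.3 and N 154. With fewer RWG infants precision is lower and the rate is higher.

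**The case against.** The strongest reply is that the article never says windows will be declared from age-by-age p-values. The critical-period sentence describes what the method can do, and the significance sentence is general. Read literally, model (1) gives one β_v per variable and no curve to inspect. If the β coefficients are spline terms, the non-constant ones do bear on time variation. A reader might infer that the authors have committed to reading windows off a pointwise curve; the text does not support that, so the simulated rates are conditional on such a reading. What remains is that on none of these readings does the article state a test of constancy, although it does state an inferential rule and a timing conclusion.

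A second reply is that Aim 1, as hypothesised, concerns association, for which β = 0 is the right null. That is correct. A reader might infer that the main Aim 1 analysis is unsound, and this point does not show that.

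A third reply is that the size is fragile. The simulation uses simple polynomials and free visit effects in place of a penalised spline, and sleep levels where the article refers to changes between visits. RWG prevalence is assumed. The protocol also mentions medium to large effects in preliminary data, and with strong effects the problem largely recedes. All of this stands, and it is why a range is given. A general statement that constant effects would often be reported as windows goes too far: it holds near the Aim 1 effect size, not at an OR of 2 per SD.

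**Conclusion.** The point holds as a mismatch between a stated conclusion and the only stated test. The plan expects to find critical periods and to act on them, but its rule tests for no effect and never asks whether the effect changes with age. The association hypothesis of Aim 1 is untouched.

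If windows were read from where the curve is significant, a constant effect of one third of an SD would look like a window in roughly 28-73% of studies. The range reflects mainly curve flexibility, under assumed prevalence 0.2-0.5 and correlation 0.5. The rate falls to about 1-14% at an OR of about 2 per SD, with prevalence about 0.3. A constancy test declares time variation in about 4-8% when there is none. The change is worth making before analysis, and the article reports recruitment and follow-up as ongoing.

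**What to change.** Add to the Aim 1 analysis:

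> A critical period will be claimed for a sleep variable only if a joint test of the time-varying terms of β_v(t) against a time-invariant β_v, allowing for within-infant clustering, rejects at α = 0.05. Otherwise the overall coefficient is the main result, and the age-specific curve with its confidence band is shown as descriptive only.

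Model (1) already supports both fits, since moving the variable from V to C gives the time-invariant version. Use this one test and do not offer a lower AIC as an alternative. With two extra terms, AIC prefers the varying model whenever the likelihood-ratio statistic exceeds 4, which under constancy has probability exp(−2) = 13.5% and not 5%. Offering both would also leave the choice open after the data are seen.

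The cost is one extra fit per sleep variable and no new data. The constancy test will have limited power at this sample size, so a real window may go unclaimed. A non-significant result should therefore not be reported as proof that timing is irrelevant.

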**Methods:**

The Snuggle Bug/ Acurrucadito study is an observational, longitudinal study investigating whether 24-h, actigraphy-assessed, sleep-wake patterns and GM development are associated with RWG among infants in their first year. Based on the Ecological Model of Growth, we propose a novel conceptual framework to incorporate sleep-wake patterns and the GM as metabolic contributors for RWG in the context of maternal-infant interactions, and familial and socio-physical environments. In total, 192 mother-infant pairs will be recruited, and sleep-wake patterns and GM development assessed at 3 and 8 weeks, and 3, 6, 9, and 12 months postpartum. Covariates including maternal and child characteristics, family and environmental factors, feeding practices and dietary intake of infants and mothers, and stool-derived metabolome and exfoliome data will be assessed. The study will apply machine learning techniques combined with logistic time-varying effect models to capture infant growth and aid in elucidating the dynamic associations between study variables and RWG.

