## Background

### Early rapid weight gain in infancy contributes to childhood obesity

Early childhood obesity is a serious health problem. In 2019, 38.2 million U.S. children less than 5 years old were overweight or obese, with greater prevalence among low- and middle-income families [1]. Of those under 2 years, 8.1% had high weight-for-recumbent length (i.e., at or above the 95th percentile) [2]. Further, obese children are more likely to become obese adults [3]. Rapid weight gain (RWG) in the first 6 months of infancy, defined as a greater than 0.67 positive change in weight-for-age Z-score (difference between centile lines on standard growth charts) [4], is associated with greater total weight gain from 0 to 12 months and greater weight-for-length and weight-for-age percentiles at 36 months [5]. It also increases the odds of obesity across the life course [6–9] and relates to adverse health outcomes later in life, including hypertension, diabetes, and cardiovascular diseases [10]. Further, RWG in the first 3 months is more predictive of poor cardiometabolic outcomes than any other 3-month period in the first year of life [11]. Despite robust, globally diverse cohort data accounting for numerous confounding factors present from conception to birth on childhood obesity, few studies have focused on RWG determinants and timing in the birth-to-6-month period.

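### Model (1) gives marginal age-specific associations with RWG, so its coefficient p-values cannot by themselves single out a critical period

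*Protocol article*

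**What the plan says.** The outcome is fixed per infant: "Rapid weight gain (RWG) in the first 6 months of infancy, defined as a greater than 0.67 positive change in weight-for-age Z-score". The exposures are repeated: "sleep-wake patterns and GM development assessed at 3 and 8 weeks, and 3, 6, 9, and 12 months postpartum".

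Under Statistical analyses, model (1) writes logit(RWG) as a smooth time-varying intercept, plus variables V with smooth time-varying coefficients, plus covariates C with constant coefficients. For Aim 1, the sleep variables enter as visit-to-visit changes. Aim 2 reuses the model for gut microbiota. Significance is read from the p-values of the estimated coefficients. No term for the same variable at another age is described.

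Two statements draw a timing conclusion from this model. Under Statistical analyses: "It can reveal critical periods during which changes in sleep-wake patterns accelerate/decelerate infant weight gain". In the Discussion: "identification of optimal and crucial developmental intervals for targeting and preventing RWG".

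The only correlation given for the repeated measures is in the Aim 1 power paragraph: "a correlation among the repeated measures of 0.5, a compound symmetry structure".

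**The concern.** RWG does not vary over time within an infant. When the same yes/no value is related to exposure at age t, without that infant's exposure at other ages, the coefficient answers whether exposure at t is associated with RWG. It does not answer whether exposure at t matters once the other ages are accounted for. A claim about a critical period needs the second answer.

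If exposures at different ages are correlated, an effect that acts at one age shows up at others, and the p-values at those ages reject for that reason. With changes the distortion takes a particular form: a harmful change makes its neighbours look protective. That resembles the accelerate/decelerate pattern the article proposes to interpret. At stake is which ages are offered as targets for prevention.

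**Working it through.** **Source of the correlation.** The 0.5 comes from the Aim 1 sample size: "equal sample sizes, 6 time points", "a medium effect size of one third of a standard deviation, an α of 0.05, and a power of 0.8", giving "a total sample size of 184 participants (includes for estimated 20% attrition) is needed for Aim 1". Take n per group = 2(z_α + z_β)²(c′Σc)/(c′δ)², with a linear-trend contrast c, compound symmetry at 0.5, and a group difference growing from 0 to 1/3 SD.
- One-sided α, actual visit months: total 146.0, and 146.0/0.8 = 182.5.
- One-sided α, equal spacing, retention falling to 80%: 180.0.
- Two-sided α with attrition: 214 to 252.

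So 184 is reproduced within 3% on a one-sided reading (the article does not state sidedness). This point does not dispute that figure; it only takes r = 0.5 from it.

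**Levels.** If only V_s acts, with log-odds b, then E(V_s | V_t) = r·V_t, so the coefficient of V_t alone is about r·b (slightly less on the logit scale). A simulation with n = 1,000,000, an effect of 0.693 at 3 months only, and RWG about 29% (effect and share assumed) gives:

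| Correlation | 3 wk | 8 wk | 3 mo | 6 mo | 9 mo | 12 mo |
|---|---|---|---|---|---|---|
| CS 0.5 | 0.32 | 0.32 | 0.69 | 0.32 | 0.32 | 0.32 |
| AR(1) 0.5 | 0.16 | 0.32 | 0.69 | 0.32 | 0.16 | 0.08 |

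Under compound symmetry, 0.32/0.693 = 0.46. With r = 0.3 the copies are 0.19 and with r = 0.7 they are 0.46, about 0.28 and 0.67 of the effect. With r = 0 they vanish. All six visits entered together at r = 0.5 give 0.695 at the true age and −0.007 to 0.002 elsewhere.

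**Visit-to-visit changes.** Under compound symmetry:
- Cov(V2−V1, V3−V2) = r − 1 − r + r = r − 1, and each change has variance 2(1−r).
- The correlation is therefore (r−1)/(2(1−r)) = −0.5, whatever r is.
- Non-adjacent changes: r − r − r + r = 0.
- Under AR(1), adjacent changes correlate −(1−r)/2, which is −0.25 at r = 0.5.

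The simulation agrees. A true effect on the 8-week to 3-month change alone gives −0.32, 0.69, −0.33, 0.00, 0.00 over the five intervals. If instead the 3-month level is what acts, the changes show 0.00, +0.32, −0.32, 0.00, 0.00.

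**How often wrong ages are flagged.** Setting: 192 × 0.8 = 153.6, so 154 infants; four visits to 6 months; r = 0.5; log-OR 0.5; RWG about 30% (last two assumed). The fit is stacked and smooth in t, with cluster-robust errors.
- Changes: neighbours about −0.25; a wrong interval flagged in 45% of studies, against 9% with joint fitting.
- Levels: at least one null age flagged in about 65%, against 13% with joint fitting.
- Levels fitted visit by visit without smoothing (RWG 20–40%): 32–53%, against 8–14% jointly. The rate thus depends on smoothing and RWG share.

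The joint rates are what 5% tests would give: 1 − 0.95² = 9.8% for two null intervals and 1 − 0.95³ = 14.3% for three null ages, if independent.

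**Where the peak falls.** Six visits, n = 160, r = 0.5, levels, unsmoothed. Largest z at a wrong age:

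| Odds ratio | Model (1) type, one age per coefficient | Joint |
|---|---|---|
| 1.5 | 39% | 44% |
| 2.0 | 11% | 13% |
| 2.5 | 3.5% | 4% |

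Joint fitting removes the false flags but does not locate the peak better.

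**Price of joint fitting.** Variance inflation is 1/(1−R²). For levels at r = 0.5, it is 1/(1−0.333) = 1.5 with three visits and 1/(1−0.375) = 1.6 with four, so standard errors are 22–26% wider. For the middle of three changes, R² = 0.25 + 0.25 = 0.5, inflation is 2, and √2 means 41% wider. In the 154-infant setting, power at the true age falls from about 78% to 50–58%.

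**The case against.** **Aim 1 is framed as association.** A marginal model answers that question, and this stands: the overall test is not affected. But the same section says the model can reveal critical periods, and the Discussion carries that forward. It is this inference that does not follow.

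**A condensed article leaves V and C general.** Earlier exposures could in principle be among them. But V is described as a set of variables, not as one variable's history, and the timing claim is attached to the model as printed.

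**The plan smooths across ages and does not fit each visit separately.** True, but smoothing adds no adjustment for other ages, and the stacked smooth fit still flags wrong ages often.

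**Stronger readings a reader might infer.**
- *The wrong interval will be named.* Not supported in general: without smoothing, the true age keeps the largest expected coefficient. With a stacked spline at n = 160 and odds ratio 2, the peak fell at a wrong visit in 7% to 97% of runs, depending on flexibility and the true age. That blurring comes from smoothing six visits on top of the correlation, so no single figure can be set on it.
- *A half-size copy appears at every age in Aim 1.* This describes levels. The article states changes, where the copy is reversed in sign and, under compound symmetry, limited to adjacent intervals.
- *The same 0.5 holds for gut microbiota.* The article gives no correlation for it.

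**Joint fitting is not neutral.** It conditions early exposure on later exposure. If early sleep acts partly through later sleep, the joint coefficient leaves that part out. This stands, and is why both curves should be reported.

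**Conclusion.** The point holds in a limited form. As written, model (1) yields marginal, not mutually adjusted, age-specific associations with a single RWG value per infant. Its coefficient p-values flag additional, wrong intervals far more often than 5%, so they do not isolate a critical period.

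That the coefficients are marginal follows from the printed model and the outcome definition. The size of the carry-over rests on a compound-symmetry correlation that is only an Aim 1 planning value. Under AR(1) it is smaller at distant ages for levels, and smaller between adjacent intervals for changes. The flag rates also rest on an assumed effect size and RWG share. They should be read as showing a large excess, not as error rates of this study.

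**What to change.** 1. Under Statistical analyses, keep model (1) for the overall association and describe its coefficient curve as marginal.
2. Before naming any critical period, also fit one row per infant: logit P(RWG) = a + Σ_k b(t_k)V_k + covariates. Enter the exposures of all visits up to the 6-month outcome together, with b(t) smooth or penalised. Require support from this model. State whether the 6-month recording, which is worn after that visit, counts.
3. Report the marginal and joint curves side by side.
4. If the joint model is not wanted, reword the critical-period sentence under Statistical analyses and the closing claim in the Discussion as age-specific marginal associations.

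The cost is wording and one extra model, with no new data; recruitment was still under way when the article was written. State the downsides in the plan: wider standard errors and lower power at the true age, no better location of the peak, missed visits that must be imputed where the stacked model uses whatever visits exist, and early coefficients that exclude any effect acting through later exposure.

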### Aim and design

This study is designed as a five-year observational longitudinal study to investigate how 24-h sleep-wake patterns and GM influence RWG among infants in their first year. In this study, we aim to:
Investigate associations of infant sleep-wake patterns with subsequent RWG at 6 months and weight gain at 12 months using Time-Varying Effect Models (TVEM). We hypothesized that infants with suboptimal sleep-wake patterns (e.g., short sleep duration, poorer sleep quality [e.g., sleep percent, number of long awakenings], later bedtimes, and greater sleep-wake timing variability) will be more likely to experience RWG at 6 months and have greater total weight gain at 12 months than infants with optimal sleep-wake patterns.Investigate associations of GM development with RWG at 6 months and weight gain at 12 months. We hypothesized that infants with lower GM diversity, decreased relative abundance of beneficial microbes (e.g., *Bifidobacteria*), and increased pathogen abundance (e.g., *Staphylococcus*) across time will be more likely to experience RWG at 6 months and have greater total weight gain at 12 months.Evaluate whether temporal interactions exist between infant sleep-wake patterns and GM development, and if these relations influence RWG. We hypothesize that (1) infants with short sleep duration, poorer sleep quality, later bedtimes, and greater sleep-wake timing variability will exhibit lower GM diversity, decreased relative abundance of beneficial microbes, and increased pathogen abundance than infants with optimal sleep-wake patterns; and (2) infant sleep-wake patterns and GM development will have a synergistic effect on RWG, with suboptimal development of both factors increasing risk for RWG compared to either factor independently.

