To evaluate Aim 3, exploratory analysis will apply principal component analysis to examine if the combination of GM variables and sleep-wake variables can explain a higher variance of RWG than using each class of variables independently. Confirmatory analysis will use model (1) to include the main effects and pairwise interactions between GM diversity scores and sleep-wake variables. Significant p-values and positive coefficients of interaction terms will indicate synergistic effects. However, because there are potentially many GM taxa associated with RWG, model (1) may include too many variables and trivial effects that reduce the statistical power. In this case, we will take a nested approach to test synergies among correlated variables. Specifically, combining the significant variables identified in Aims 1 and 2, we will first test pairwise correlations. We will then group significantly correlated variables using Gaussian finite mixture models [117] that automatically determine the number of clusters. If GM diversity scores and sleep-wake patterns coexist in a cluster, we will use model (1) extended with interaction terms to test synergistic effects. For the proposed exfoliomic data, we will utilize systems biology approaches to illuminate transgenomic cross-talk between host exfoliated intestinal epithelial cells [84] and the genomes of the gut microbiota [83, 118] in a longitudinal cohort.

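### The exploratory Aim 3 criterion, that sleep and GM together explain more RWG variance than either alone, is uninformative as written

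*Protocol article*

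**What the plan says.** Under Statistical analyses, the protocol article splits Aim 3 into two steps. In the first, "exploratory analysis will apply principal component analysis" to examine whether GM and sleep-wake variables combined "can explain a higher variance of RWG than using each class of variables independently". The sentence gives no number of components, penalty, test or held-out comparison; the criterion is simply a higher value.

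The second step is separate: "Confirmatory analysis will use model (1) to include the main effects and pairwise interactions between GM diversity scores and sleep-wake variables". It has its own decision rule: "Significant p-values and positive coefficients of interaction terms will indicate synergistic effects".

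The hypothesis being served, under Aim and design, is that "infant sleep-wake patterns and GM development will have a synergistic effect on RWG", with greater risk when both factors are suboptimal than with either factor alone.

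**The concern.** Two features of the stated criterion cause difficulty.

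- **Method and target do not match.** PCA decomposes the variance of the predictors and takes no account of the outcome. Nothing is said about RWG until it is regressed on the retained components, a step the sentence leaves implicit.
- **A higher value is a weak bar.** Once that regression is done, a set with more components generally fits the data at hand better, whether or not any variable is related to RWG.

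An exploratory analysis should still be able to return a no. The wording also runs close to the Aim 3 hypothesis, which contrasts both factors with either one alone, so a nearly automatic yes could be read as early support for it.

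**Working it through.** The plan gives no figure for this comparison, so there is none to reproduce. The question is how often the stated criterion is met when nothing is related to RWG.

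**Inputs from the protocol article**
- Analysable infants: n = 160 (Power analysis and target population: "160 infants are required to achieve a power of 0.8").
- Sleep-wake variables: 5 actigraphy + 4 cosinor + 5 non-parametric rhythm variables = 14, counted from Assessment of sleep.
- Outcome: binary RWG, modelled by logistic regression (Statistical analyses).

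**Assumptions, because the article gives no figure**
- RWG rate of 20% or 30%.
- 20 or 60 GM variables (the article speaks only of hundreds of taxa).
- Three latent factors per class, and one record per infant.

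**Method.** RWG was generated independently of every predictor, with 300-500 data sets per setting. Logistic models were fitted on the components of sleep, GM and both. Fit was measured in-sample by deviance R² = 1 − D(model)/D(null). A spurious win means that the combined R² exceeds both single-class values.

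**Spurious wins with no true association**

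| How components are chosen | Spurious wins |
|---|---|
| Class components pooled (3+3 or 5+5) | 100% |
| PCA on all variables, twice as many components as each class | 89-95% |
| Kaiser rule (eigenvalue above 1) | 93-96% |
| Kept to 80% of predictor variance | 86-94% |
| Kept to 70% | 81-89% |
| Kept to 50% | 70-83% |
| Same number (2, 3 or 5) in every set | 20-28% |

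A further set of runs at 25% RWG gave 80-97% under the Kaiser, 50% and 80% rules, and 23-27% with equal counts. Across both sets, the usual retention rules therefore span roughly 70-97%.

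**Check by hand for the pooled case.** The combined model contains each single-class model, so its deviance cannot be higher and the 100% is a certainty. With three components per class, adding the other class lowers the deviance by approximately a χ² variable on 3 degrees of freedom under the null. The gain over the better class is the smaller of two such independent drops, with mean about 1.73. At n = 160 and 30% RWG, D(null) = −2 × 160 × (0.3 ln 0.3 + 0.7 ln 0.7) = 195.5. The expected spurious gain is 1.73/195.5 = 0.009, close to the simulated 0.009-0.010. Over all the settings that favour the combined set, the mean spurious gain was small, about 0.006-0.033.

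**With a penalty, a test or held-out data (pooled 3+3 case)**
- AIC: both drops must exceed 2 × 3 = 6. P(χ²₃ > 6) = 0.112, and 0.112² = 0.012. Simulated: 1.3-2.3%.
- Likelihood-ratio tests against both single-class models at 0.05: 0.05² = 0.0025. Simulated: 0-0.3%.
- Five-fold cross-validated log-likelihood, simulated: 7-11%.

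**The case against.** The strongest reply has four parts.

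1. **The step is labelled exploratory.** Synergy is decided by the interaction terms of the confirmatory model. A reader might infer that the main conclusion of Aim 3 would rest on the PCA comparison. The document does not support that, because the next sentences assign the conclusion to another analysis with its own rule. This part stands and limits the consequence.
2. **The result depends on a retention rule that the article does not state.** A reader might infer that the combined set must win by construction, or that the comparison cannot come out negative. That is true only when class components are pooled. Components from PCA on all variables together do not contain the class-specific ones, and with equal counts the combined set loses in 72-80% of null data sets. This part also stands. It does not rescue the criterion, since a yes in a fifth to a quarter or more of null data sets, with no test attached, is still not evidence.
3. **A condensed article may leave component numbers and validation to the full protocol or analysis plan.** That is fair, and their absence is not the point. The point is the criterion the article does state. The same section names safeguards elsewhere: false discovery rates and AIC ranking for Aim 2, and p-values for Aim 1 and the confirmatory part of Aim 3.
4. **Regressing an outcome on components is routine, and the spurious gain is small.** Both are true. The first makes the PCA wording loose rather than unworkable. The second does not help, because the criterion sets no minimum gain.

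**Conclusion.** The point holds for the exploratory criterion as worded. With an unpenalised in-sample comparison, a higher explained variance for the combined set is certain if class components are pooled. With nothing related to RWG, it occurs in roughly 70-97% of data sets under usual retention rules and in about 20-28% with equal component counts. These rates rest on the assumed RWG rate, number of GM variables, factor structure and one record per infant. Varying the RWG rate from 20% to 30% and the GM variables from 20 to 60 did not change the pattern, whereas the retention rule changes it greatly.

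The consequence is limited to the exploratory statement. The synergy conclusion belongs to the confirmatory interaction model and is untouched. Even a true rise in explained variance would show that the two classes contribute additively, not that they act synergistically.

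**What to change.** Replace the higher-variance criterion by a penalised or held-out comparison of three logistic models for RWG: sleep components, GM components, and both. Either of these would serve:

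- AIC, which the plan already uses to rank taxa in Aim 2, or likelihood-ratio tests of the combined model, built by pooling the class components, against each single-class model.
- Cross-validated deviance, with folds split by infant and components derived within each training fold.

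State that any gain is described as joint (additive) prediction only, and that synergy is judged solely from the confirmatory interaction terms.

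The cost is a change of wording and modest computing, with no new data. The reported gain will be smaller than the in-sample one.
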